## Abstract

**Background:**

Among food pantry users there is a high prevalence of both smoking and food insecurity, which may be related to one another. This study aims to evaluate the impact of a smoking cessation program carried out in food pantries on the smoking status and the food security status of food pantry users.

**Methods / design:**

Before starting the cluster randomised controlled trial, stakeholders will be engaged to adapt a behavioural group counselling program for smoking cessation to the needs of the food pantry users in a pre study. Food pantry users and workers as well as other experts, such as smoking cessation trainers, social workers, and psychologists, will be involved, using the world café technique and telephone interviews and a qualitative thematic analysis for data analysis to design the concept of the intervention program will be applied. In the second phase, the impact of the intervention on the smoking status and on food insecurity will be investigated by a cluster randomised controlled trial. A total of 416 food pantry users across 32 clusters (food pantries) in Berlin, Germany, should be recruited and randomly assigned to either the intervention group or the waiting list control group. The intervention will consist of a behavioural group counselling program for smoking cessation, specially tailored for food pantry users, as well as optional nicotine replacement therapy and the implementation of environmental smoking reduction measures in the food pantries. The primary outcomes 6 months after the treatment will be self-reported continuous smoking abstinence, validated by exhaled carbon monoxide (< 10 ppm of carbon monoxide), and increased food security level (the percentage of participants with an improved food security level).

**Discussion:**

This study will be the first long-term investigation into the effect of a smoking cessation program on smoking status and food insecurity. The results of this study will inform the implementation of smoking cessation programs in food pantries throughout Germany.

**Trial registration:**

Prospectively registered DRKS00020037. Registered 29 April 2020

## Background

Smoking is one of the major risk factors of mortality and morbidity in Germany [1] and accounts for around 125,000 premature deaths per year [2]. In addition to individual burden, smoking causes social costs of 79 billion euros per year [3].

Although the health risks of smoking are well known, around 28% of the population were reported to smoke in 2016 and 2017 in Germany [4]. Similar to other developed countries [5], smoking is not equally present among all demographics, but has become increasingly concentrated among low income population groups. For instance, from 1998 to 2014, the prevalence of smoking decreased in most income groups, whereas it increased to nearly 34% among the population group in the lowest income quartile [6]. Over the last decades, socio-economic differences in smoking behaviours have become one of the major contributors to existing socio-economic disparities in quality of life, morbidity and mortality [7, 8].

One population group at a particularly high risk of smoking is food pantry users. Food pantries are charitable organizations that distribute surplus food donated from food banks, retail stores, and manufacturers to those in need [9]. Although food pantry users are heterogeneous in terms of their educational background, age, and household size, one commonality is low income [10]. In previous studies in Germany, the prevalence of smoking was higher among participating food pantry users, at around 37% [11] and 47% [12], compared to others with low income. Similar or even higher smoking prevalence was found among food pantry users in other European countries [13, 14].

An additional concern is the observed high prevalence of food insecurity among food pantry users [11, 13–15]. Food insecurity exists “whenever the availability of nutritionally adequate and safe foods or the ability to acquire acceptable foods in socially acceptable ways is limited or uncertain” [16]. Food insecurity is related to dietary quality [17, 18] as well as the risk of several chronic diseases such as obesity, diabetes mellitus and depression [19, 20]. In a previous German study, around 70% of over 1000 food pantry users were reported to be food insecure, of which around 28% were moderately and 8% were severely food insecure [11]. In contrast, the Food and Agriculture Organization of the United Nations estimated that around 4% of the population was mildly or severely food insecure in Germany [21].

Thus food pantry users suffer disproportionately more from two considerable health risks, smoking and food insecurity, compared to the general population. Importantly, these health risks may be related, as recent studies among socio-economically disadvantaged individuals [22] and food pantry users [23] have found a significant relationship between smoking status and food insecurity, even when controlling for income or other socio-economic characteristics. For instance, a cross-sectional trend analysis demonstrated that in the USA from 1998 to 2011 the prevalence of food insecurity increased more among smokers compared to non-smokers [24]. One of the reasons might be that smokers with a low income use a disproportionately larger share of their income for cigarettes and other tobacco products than their wealthier counterparts [25]. This share of income is then not available for food. The struggle to afford both food and tobacco products might therefore increase the risk of food insecurity. In particular, among low-income individuals such as food pantry users, stopping smoking might lead to a significant relief of pantry users’ budgets and might, therefore, improve food security.

Several smoking cessation programs exist in Germany to assist people in stopping smoking [4]. As demonstrated by an international review, group behavioural therapy programs for smoking cessation are more effective than self-help [26]. However, only 12.5% of smoking cessation attempts are reinforced by evidence-based methods in Germany [4], which is considerably low compared to other countries [27]. Given that attempts to quit smoking without appropriate support have less chance of success (only 3–5% of self-quitters succeed in the long term [28]), a national health objective is to increase the use of evidence-based methods by implementing setting-based smoking cessation programs [29].

While smokers with low income do not differ in their usage of evidence-based smoking cessation methods from their wealthier counterparts [30], they succeed less often in smoking cessation in Germany [6, 31] and elsewhere [5]. Psychosocial factors contributing to these differences include lack of support, greater addiction to tobacco, and less motivation to quit [5]. However, as illustrated above, food pantry users might differ even from general low-income populations, and psychosocial factors related to smoking and smoking cessation among food pantry users are widely unknown. As a consequence, there is no smoking cessation program adapted to the needs of food pantry users.

Addressing both challenges, the low usage of smoking cessation programs and the lack of smoking cessation programs adapted to the needs of food pantry users, we will first adapt a smoking cessation group program according to the needs of food pantry users by stakeholder engagement and qualitative research. Then we will investigate the impact of this group program, when provided in parallel with nicotine replacement therapy and the implementation of environmental smoking reduction measures in the food pantries, on the smoking prevalence and food security among food pantry users in Berlin through a cluster randomised controlled trial.

## Objectives and hypotheses of the study

The main objective of the study is to investigate the impact of the smoking cessation measures on the smoking prevalence and on food security among food pantry users in Berlin.

The following primary hypotheses will be tested:
The percentage of individuals displaying continuous smoking abstinence 6 months after the treatment will be higher in the intervention condition compared to the control condition.The percentage of participants with an improved food security level 6 months after the treatment will be higher in the intervention condition compared to the control condition.The increased food security level will be mediated by continuous smoking abstinence.

Important secondary objectives include
to assess the impact of the smoking cessation measures on other measures of smoking status (point prevalence of smoking abstinence, the mean number of cigarettes smoked per day) and of food insecurity (the mean number of affirmative responses on the FIES) as well as on the health-related quality of life scores and body-mass-index;to investigate whether possible intervention effects are moderated by demographics (age, gender, migration status, socioeconomic status), the nicotine dependence and time perspective.

## Methods / design

### Setting

Both the stakeholder engagement and the cluster randomised controlled trial will be conducted with the charitable organization the “Berliner Tafel” (“Berlin table”). At its start, the “Berliner Tafel” collected surplus foods from retailers and manufacturers and distributed these foods to social organizations such as women’s refuges, kids clubs, and homeless shelters. Since 2004, the “Berliner Tafel” has provided groceries to clients at 45 food pantries mainly located in religious establishments [32]. Those who fulfil the eligibility criteria defined by the “Berliner Tafel”, i.e. have an income at or below the level of the federal unemployment benefit II, are allowed to take groceries such as fresh fruits, vegetables, and bread for a small fee of one or two euros once a week or every second week [33]. Eligible individuals are allocated to one of the food pantries by officials of the “Berliner Tafel”, mostly according to residents’ postal code [33].

### Pre-study: stakeholder engagement to develop the intervention

Before starting the cluster randomised controlled trial, stakeholders will be engaged to develop a behavioural group counselling program for smoking cessation adapted to the needs of the food pantry users. The interventional group program is planned to be based on the existing evidence-based behavioural counselling smoking cessation program called “Rauchfrei” (“smokefree”) [34]. The needs of the food pantry users will be explored qualitatively in interviews and group discussions.

The original “Rauchfrei” program was developed by the Institute for Therapy Research in Munich and the German Federal Centre for Health Education (Bundeszentrale für gesundheitliche Aufklärung) and is the most widespread cognitive behavioural group program for smoking cessation in Germany [34]. The original program consists of 3 to 6 weekly meetings with other participants and the “Rauchfrei” trainer along with individual telephone-based counselling [35].

The methods of behavioural modification used consisted of cognitive strategies to change attitudes, motivational interviewing, strategies of goal orientation, and psychoeducation as well as the development of coping skills to deal with cravings and relapses. The program includes a fixed date to quit smoking in the middle of the program [35].

To identify the target group’s needs, the World Café technique [36] was chosen. One World Café with around 15 food pantry users, aged at least 18 years, will be conducted in a Berlin food pantry. Food pantry users will be recruited by leaflets, posters, and personal invitations from trained staff. The World Café will be conducted as follows: firstly, participants will be recruited through direct contact with a recruiter at their food pantry who will provide an informational brochure. They will be informed about the study’s aim and procedure, as well as about data protection regulation, verbally and with a written information sheet. If the pantry users are willing to participate they will be given a written consent form and, after signing it, will fill in a short questionnaire regarding demographics, smoking status, and including the quantity-frequency index [37]. The moderator will introduce participants to the World Café technique. Then groups of four or five participants will sit around four tables, together with a table host, and they will discuss freely predefined questions around the following four themes: 1. intentions and advantages of stopping smoking 2. barriers to stopping smoking 3. facilitators of stopping smoking 4. support from the food pantry to stop smoking. Each table host will have a different set of open-ended questions relating to one of these four main themes. After 20 min discussion participants will change the table and mix up to a new group. Participants will be encouraged to record or doodle their thoughts, comments, and questions on a white paper tablecloth. The table host will help the group to keep on topic and encouraged participation from all participants. At the end of the World Café, the hosts will present a summary of the discussions and all participants will discuss and reflect the findings.

Initially, an additionally second world café with around ten “Rauchfrei” trainers, food pantry managers, social workers, and psychologists was planned. Due to the ongoing COVID-19 pandemic, and the implementation of social distancing measures throughout Europe [38], semi-standardised phone interviews which each person alone will be conducted instead. The interview guide will contain the four main themes previously discussed by food pantry users during the World Café, as well as the experts’ concerns and knowledge in regards to food pantry users, smoking and smoking cessation. The formulation of the four main topics will be slightly adapted accommodate outsider perspectives on the situation of food pantry users. Food pantry users and managers participating in the formative study will receive a €20 voucher for an electronics shop or a clothing store.

Both the interviews and World Café discussions will be audio recorded digitally, transcribed, and will be analysed qualitatively by conducting thematic analysis with MAXQDA software (2018). In the next step themes and concepts relevant for smoking cessation in the context of food pantry users will be identified and then addressed through adaptations of the existing basic behavioural counselling smoking cessation program.

The results of the qualitative analysis will be discussed with experienced facilitators of smoking cessation programs in order to receive feedback. Based on the results of the qualitative analysis, relevant recent research, and the needs of the food pantry users, the behavioural group counselling intervention program for smoking cessation will then be designed.

### Study design

After the pre-study, a pragmatic two-arm cluster randomised controlled trial, targeting approximately 32 food pantries in Berlin, will be conducted. Cluster randomisation is used to minimise the risk of carryover effects from the intervention to the control group. Data among food pantry users will be assessed on the date of study inclusion (t0), 1 month after completing the smoking cessation program (t1), and 6 months after completing the smoking cessation program (t2) (see Fig. 1). The control group will receive the smoking cessation program after the intervention group has completed the program (waiting list control group).

**Fig. 1 Fig1:**
[figure not shown]
Flow chart of design and measurements

### Study population

The study population will include users of any of the participating food pantries who reported smoking at least one cigarette or cigarillo per day. Participants must be at least 18 years old and able to sufficiently understand and speak German. Exclusion criteria includes non-smokers and individuals who smoke less than daily as well as individuals who do not use any of the participating food pantries. In addition, individuals who are 17 years of age or less, are unable to understand and speak German, or are illiterate, will also be excluded. Finally, individuals who only use e-cigarettes or tobacco heating systems will be excluded, since the impact of the original “Rauchfrei” program on this form of tobacco consumption is currently unknown.

### Procedures

#### Recruitment of the food pantries and randomisation

In consultation with the coordinator of the food pantries, all the “Berliner Tafel” food pantries will be invited to participate in the study by letters of invitation. Personal invitations will follow in case of no response.

Food pantries whose managers agree to participate via written consent will be randomly allocated to the intervention or control group by means of permuted block randomisation with randomly varying block sizes. The intended allocation ratio is 1:1. The randomisation lists will be computer generated. The team member conducting the randomization will be involved neither in recruitment of participants nor in data collection.

Given that participating food pantries will provide rooms for conducting the study for free, the pantries will be entered into a raffle for ten fuel vouchers valued at €50 each.

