### Sample size

The required sample size was calculated using the function n4prop in the package CRTSize developed for the program R (version 3.3.2) [47].

In a previous study, the smoking status of users of eight food pantries in Berlin was assessed [11]. The number of participants per food pantry in Berlin was, on average, 56 ± 12 (ranging from 36 to 73) and the number of smokers was, on average, 26 ± 8 (ranging from 19 to 41). A systematic review of recruitment strategies of smoking cessation studies revealed that studies using “active strategies” (i.e. interpersonal contact with the research team or program provider) reached from 47% up to 84% of eligible individuals, with lower participation rates among low-educated populations [48]. Therefore, a participation rate of 50% and a sample size per cluster of *n* = 13 will be assumed.

Based on the results of previous studies [49], cessation rates of 10 and 3% are assumed among participants in the intervention group and the control group, respectively.

Assuming an intra-class correlation coefficient of 0.02, a 5% significance level, and 80% power, 32 clusters are needed to detect an effect (16 in the intervention group and 16 in the control group).

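### The 32 pantries are allocated in blocks that balance only their number; stratifying on pantry size would cheaply reduce the chance of uneven arms, with a gain in precision if size is related to outcome.

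*Protocol article*

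**What the plan says.** The section *Recruitment of the food pantries and randomisation* makes the pantry the unit of allocation. Consenting pantries are "randomly allocated to the intervention or control group by means of permuted block randomisation with randomly varying block sizes", from computer-generated lists, and "The intended allocation ratio is 1:1". Block sizes are not given, and no stratum, matching or constraint is named.

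The section *Sample size* plans 13 participants per pantry and an ICC of 0.02, and concludes that "32 clusters are needed to detect an effect (16 in the intervention group and 16 in the control group"). It also reports an earlier survey of eight Berlin pantries. Participants per pantry were "on average, 56 ± 12 (ranging from 36 to 73"), and smokers per pantry were "on average, 26 ± 8 (ranging from 19 to 41").

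The section *Statistical analyses* plans a chi-square test adjusted for intraclass correlation and mixed models with a logit link. Neither is said to include a pantry-level covariate.

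**The concern.** With only 16 pantries per arm, balancing the count leaves a real chance that the arms differ in the kind of pantry they contain. Size is the one pantry characteristic for which the article gives figures, and it varies about twofold. A client count could be requested when the manager consents, which is before allocation.

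Size could plausibly matter. It may affect how many people join a counselling group, or who is found in the queue at the two follow-up visits described under *Study procedure*. These are inferences, and the article does not make either link.

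Allowing for clustering puts between-pantry variation into the standard error, but it does not correct an imbalance that has occurred. At stake are some precision and the credibility of the comparison if the arms turn out visibly unequal.

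**Working it through.** **Inputs from the article.** 32 pantries, 16 per arm, 13 participants each (32 × 13 = 416, the stated total); ICC 0.02; participants per pantry 56 ± 12 (36 to 73); smokers per pantry 26 ± 8 (19 to 41).

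**Assumptions.** The trait is held by half of the pantries. Pantry size is roughly normal. The base rate of a binary outcome is 20%. The ICC of 0.02, which the article uses for cessation, also holds for that outcome.

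**1. Spread in size.** 73/36 = 2.03 and 41/19 = 2.16, so about twofold.

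**2. Chance split of a trait held by 16 of 32 pantries.** The number in the intervention arm, X, is hypergeometric (32, 16, 16).
- 10:6 or worse: P(|X − 8| ≥ 2) = 28.9%
- 11:5 or worse: P(|X − 8| ≥ 3) = 7.6%
- 12:4 or worse: 1.2%

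Simulated permuted blocks of sizes 2/4, 4/6 and 4/8 (assumed, since the article gives none) agree: 28% to 30% for 10:6 or worse, and about 8% for 11:5 or worse.

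**3. Difference in mean size between arms.** SE = SD × √(2/16) = 0.354 SD, which is 8 × 0.354 = 2.8 smokers or 12 × 0.354 = 4.2 participants per pantry.
- More than 0.5 SD (4 smokers): 2[1 − Φ(0.5/0.354)] = 15.7%
- More than 0.25 SD (2 smokers): 2[1 − Φ(0.25/0.354)] = 48%

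**4. The same after stratifying at the median.** In a simulation of 10,000 runs with 8:8 in each stratum, the chance of more than 0.5 SD is 1.5%, and of more than 0.25 SD about 23%. The median absolute difference falls from about 1.9 to 1.1 smokers per pantry.

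**5. What this is worth in variance.** The total between-pantry variance must stay within the planned ICC.
- Between pantries: 0.02 × 0.20 × 0.80 = 0.0032
- Within pantries, per pantry mean: (0.16 − 0.0032)/13 = 0.01206
- Variance of a pantry mean: 0.0032 + 0.01206 = 0.01526

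If the outcome differs by d between the two size strata, the strata account for (d/2)² of the between-pantry variance, and stratification removes that part. The ratio of unstratified to stratified variance is 0.01526 / (0.01526 − d²/4).

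| d (assumed) | d²/4 | Variance ratio |
|---|---|---|
| 0 | 0 | 1.00 |
| 5 points | 0.000625 | 1.04 |
| 10 points | 0.0025 | 1.20 |
| 11.3 points (maximum) | 0.0032 | 1.27 |

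The maximum is reached when size explains all of the between-pantry variance: d = 2√0.0032 = 0.113. The top ratio does not depend on the base rate, because it equals 1 + 13 × 0.02/0.98 = 1.27.

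**The case against.** The strongest reply is that unstratified permuted blocks with 16 clusters per arm are a valid design. Randomisation is unbiased, and chance imbalance is part of the variation that the ICC, the adjusted chi-square test and the mixed models already allow for. A pantry-level covariate could still be added in the analysis plan. No part of the article shows that pantry size predicts abstinence or food security, and if it does not, nothing is gained in precision. The size figures come from a survey of eight pantries and may partly reflect survey recruitment and not client numbers. Unequal arm totals cost little by themselves. If participants per pantry are about 13 ± 4 (half of 26 ± 8), the arm totals differ with an SD of 4 × √32 = 22.6. A difference of that size is about 219 versus 197, and the efficiency loss is 1 − (4 × 219 × 197)/416² = 0.3%.

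All of this stands. It limits the point to an improvement that is worth making because it is cheap.

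A reader might go further in three ways that the article does not support:
- **That a lopsided mix is likely.** A moderate imbalance on one trait has a chance of about 3 in 10, and a marked one about 8% to 16%. Only a small size difference, above 0.25 SD, is near an even chance.
- **That distribution rhythm is a second pantry trait to balance.** The section *Setting* says that users may collect food "once a week or every second week". It does not say that the rhythm is fixed by pantry, or how common each one is. *Study procedure* expects the next visit usually a week later, and *Strengths and limitations* reports that most users attend at least four times a month, so weekly use seems usual.
- **That an imbalance would rival the effect sought.** With d = 10 points, a 10:6 split shifts the arm difference by 10 × (10 − 6)/16 = 2.5 points. That figure rests on an assumed 20% base rate, as for food security. The planned 10% versus 3% concerns abstinence, and no target effect is stated for food security, so the two cannot be compared. Larger trait differences, such as 15 points, do not fit the plan either: 0.075² = 0.0056 exceeds the whole between-pantry variance of 0.0032.

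**Conclusion.** The point holds as a recommended improvement in design. It is neither an error nor a contradiction in the plan. As described, the allocation balances only the number of pantries, pantry size varies about twofold in the article's own figures, and no pantry-level term is stated in the analysis.

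Stratifying on size cuts the chance of a size difference above 0.5 SD from about 16% to about 1.5%. The gain in variance runs from none, if size is unrelated to outcome, through about 4% and 20% at assumed differences of 5 and 10 points, to a ceiling of about 27%. These gains rest on an ICC of 0.02 and 13 participants per pantry; the intermediate values also rest on the assumed 20% base rate. The gain in credibility needs no assumption about outcome. If a fuller protocol already names a stratification factor, the point falls away.

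**What to change.** In *Recruitment of the food pantries and randomisation*, state that the permuted blocks are run within two strata of pantry size: client number above or below the median, obtained from the coordinator or from the pantry manager at consent. Keep the randomly varying block sizes. If all pantries are allocated at one time, covariate-constrained randomisation on size is an alternative. In *Statistical analyses*, add the stratum to the mixed models. Use rhythm as a stratum only if it is confirmed to be a fixed trait of each pantry.

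The cost is one sentence on allocation, one pantry-level data item and one model term, with no change in the number of pantries or participants. There are two small drawbacks. Incomplete blocks may leave a split such as 17:15, although the present scheme can already end unequal (in 11% to 23% of simulated runs, depending on the assumed block sizes). Allocation also becomes somewhat easier to predict within strata if blocks of 2 are used.
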